### Interventions

Based on the research intervention description of the TIDieR template (27), details of the intervention protocol for the four groups are provided in Table 1. Interventions will be taken place in the physical therapy room. Participants in all four groups will receive a daily intervention, structured as five sessions per week for 4 weeks. Each session will start with a 30-min routine exercise, followed by the therapeutic intervention tailored to their group assignment: either ECHT therapy, PEMF therapy, a combination of both, or health education.

**Table 1 tab1:** The training protocol for each group base on the TIDieR template.

Item	Exercise and health education group	External application of traditional Chinese herbs therapy + exercise group	Pulsed electromagnetic field therapy + exercise group	External application of traditional Chinese herbs + Pulsed electromagnetic field + exercise group
1. Brief name	Ex + HE	EATCH + Ex	PEMF + Ex	EATCH + PEMF therapy + Ex
2. Why	1. Exercise therapy relieves knee pain at all stages of OA. Bennell et al.’s (28) study showed that a greater benefit for pain was found with a non-weight bearing quadriceps exercise program than with a weight bearing program in people with obesity. Therefore, a non-weight bearing quadriceps exercise program was adopted in our trial. 2. Patient education is vital to improve the patients’ understanding of their current condition and to ensure compliance to exercise program and long-term self-management at home.	1. The reason why to perform exercise is the same as shown in group 1. 2. Herbs have demonstrated strong anti-inflammatory and antioxidant properties, which can mitigate inflammation and reduce tissue damage. However, further research and clinical trials are essential to establish its safety, efficacy, and to explore its underlying mechanisms.	1. The reason why to perform exercise is the same as shown in group 1. 2. Recent guidelines recognize PEMF as an effective therapy for bone and cartilage pathology, capable of alleviating pain and stiffness. However, current recommendation for PEMF is moderate, primarily due to the limited duration of follow-ups in existing studies. There is a clear need for long-term studies to solidify its therapeutic potential.	1. The reason why to perform exercise is the same as shown in group 1. 2. No study has explored the combined impact of EATCH and PEMF therapy on pain alleviation and functional improvement in older adults with KOA.
3. What materials	Sand bags (ankle cuff, 0.5–5 kg) and elastic resistance bands with various color.	1. Sand bags (ankle cuff, 0.5 kg to 5 kg) and elastic resistance bands with various color. 2. Compound herbs powder, sterile gauze pad, and elastic bandages.	1. Sand bags (ankle cuff, 0.5 kg to 5 kg) and elastic resistance bands with various color. 2. The Pulsed Electromagnetic Field Therapy Device by Haobro Company, Suzhou, China.	1. Sand bags (ankle cuff, 0.5 kg to 5 kg) and elastic resistance bands with various color. 2. Compound herbs powder (as in group 2), sterile gauze pad, and elastic bandages. 3. The Pulsed Electromagnetic Field Therapy Device by Haobro Company, Suzhou, China.
4. Procedures	Participants will start the program with two sets of 10 repetitions for each exercise for the first 1 week and progress to three sets thereafter or as quickly as able. Participants will be instructed that each exercise should be performed slowly in a controlled manner. Progression will be guided by the physiotherapist at regular intervals with adjustments to participants’ ankle weights or elastic resistance bands. Participants will also be encouraged to increase the weights (0.5 kg at a time) for each exercise if they feel the exercise is “easier to complete” compared to the beginning of that week. The end position of each exercise is to be held initially for 5 s and then increased to 10 s.	The compound herbs will be finely ground into a uniform powder and thoroughly mixed. For each treatment session, 5 grams of this powder will be combined with a small amount of warm water to form a smooth, pliable paste. Then, this paste will be evenly spread onto a sterile gauze pad. The therapists will identify the most painful area of the patient’s knee, disinfect the site using 75% ethanol-soaked cotton balls, and apply the medicated gauze directly onto the affected point, securing it with elastic bandages. The application of the gauze and bandages will be kept in place for 6–8 h daily, and the local skin area will be gently cleansed with water during dressing changes.	Participants will be positioned either supine or in a long-sitting position on the treatment bed for PEMF therapy. The magnetic field will be induced using two pairs of solenoid applicators from the PEMF device. These applicators will be securely fixed to the sides of the knee with a velcroband. During each session, the PEMF parameters will be set to a frequency of 50 Hz, an intensity of 0.8 Tesla, and each session will last for 30 min. Patients will be informed that the device would not produce any noticeable noise or sensations.	Participants will perform exercises first, next receive EATCH and PEMF therapy for 30 min simultaneously. Then, The application of the gauze and bandages for EATCH will be kept in place for 6–8 h as in group 2.
5. Who provided	Experienced physiotherapists	Experienced physiotherapists	Experienced physiotherapists	Experienced physiotherapists
6. How	Exercise will be performed with a therapist: participant ratio of 1:2.	Participants will perform exercise first. Next, receive the EATCH.	Participants will perform exercise first. Next, receive the PEMF therapy.	Exercise will be performed with a therapist: participant ratio of 1:2.
7. Where	The exercise will be performed in the PT room of The Second People’s Hospital of Kunming, and the PT room of Yan An Hospital of Kunming City.	The exercise and EATCH will be performed in the PT room of The Second People’s Hospital of Kunming, and the PT room of Yan An Hospital of Kunming City.	The exercise and PEMF therapy will be performed in the PT room of The Second People’s Hospital of Kunming, and the PT room of Yan An Hospital of Kunming City.	The exercise and combined therapy (EATCH + PEMF) will be performed in the PT room of The Second People’s Hospital of Kunming, and the PT room of Yan An Hospital of Kunming City.
8. When and how much	This group will perform the strengthening exercise 30 min/day first, then receive health education for 30 min. The intervention will last 5 days/week, for 4 weeks.	This group will perform the strengthening exercise 30 min/day first, then receive the EATCH therapy. The intervention will last 5 days/week, for 4 weeks.	This group will perform the strengthening exercise 30 min/day first, then receive the PEMF therapy for 30 min. The intervention will last 5 days/week, for 4 weeks.	This group will perform the strengthening exercise 30 min/day first, then receive the EATCH and PEMF therapy simultaneously for 30 min. The intervention will last 5 days/week, for 4 weeks.
9. Tailoring	The exercises of this group can be tailored to the capacity of the participants, including: resistance, repetitions, and sets.	The exercises of this group can be tailored to the capacity of the participants, including: resistance, repetitions, and sets. The application of the gauze and bandages will be depend on the affected point of the knee.	The exercises of this group can be tailored to the capacity of the participants, including: resistance, repetitions, and sets.	The exercises of this group can be tailored to the capacity of the participants, including: resistance, repetitions, and sets.
10. How well	The assessors will be blinded to the group allocation, in order to ensure the objectivity and impartiality of the assessments.	The assessors will be blinded to the group allocation, in order to ensure the objectivity and impartiality of the assessments.	The assessors will be blinded to the group allocation, in order to ensure the objectivity and impartiality of the assessments.	The assessors will be blinded to the group allocation, in order to ensure the objectivity and impartiality of the assessments.

#### Exercise and health education group

The exercise and health education group will serve as an active control group, enabling us to determine whether the observed changes in the ECHT therapy, PEMF therapy, or their combination are a function of maturation or repeated testing. This exercise regimen, detailed in Supplementary Figure 1, was adapted from established protocols of prior studies and focused on non-weight-bearing movements in sitting or supine positions to minimize stress on the affected lower limb (28, 29). Next, participants in this group will receive an additional 30 min of health education on KOA.

#### ECHT + exercise group

The compound prescription of traditional Chinese herbs was developed in accordance with the principles of the “Inner Canon of the Yellow Emperor” and will be supplied by the Second People’s Hospital of Kunming. Details regarding the specific types and quantities of the herbs used for the external application are outlined in Table 2. These herbs will be finely ground into a uniform powder and thoroughly mixed. For each treatment session, 5 grams of this powder will be combined with a small amount of warm water to form a smooth, pliable paste. Then, this paste will be evenly spread onto a sterile gauze pad. The therapists will identify the most painful area of the patient’s knee, disinfect the site using 75% ethanol-soaked cotton balls, and apply the medicated gauze directly onto the affected point, securing it with elastic bandages. The application of the gauze and bandages will be kept in place for 6–8 h daily, and the local skin area will be gently cleansed with water during dressing changes (Figure 3).

**Table 2 tab2:** Types and quantities of the herbs used for the external application.

Types	Quantity (gram)
Pseudo-ginseng	30
Radix rehmanniae	30
Ginseng	30
Liquorice	60
Angelica sinensis	60
*Polygonum multiflorum*	30
Lotus seed	30
*Sedum sarmentosum*	60
Cattail pollen	60
Lotus rhizome node	15
Sappanwood	30
Dragon’s blood	30
Tianzhu Yellow	50
Fossil fragments	30
Albizia bark	30
Caulis polygoni multiflori	20
Rhizoma alismatis	30
American ginseng	20
Tortoise plastron	60
Glutinous rice roots and whiskers	30

**Figure 3 fig3:**
[figure not shown]
External Chinese herbal therapy (ECHT).

#### PEMF therapy + exercise group

Participants will be positioned either supine or in a long-sitting position on the treatment bed for PEMF therapy. The magnetic field will be induced using two pairs of solenoid applicators from the Pulsed Electromagnetic Field Therapy Device (Model: HB240D) by Haobro Company, Suzhou, China (Figure 4). These applicators will be securely fixed to the sides of the knee with a velcroband. During each session, the PEMF parameters will be set to a frequency of 50 Hz, an intensity of 0.8 Tesla, and each session will last for 30 min. Patients will be informed that the device would not produce any noticeable noise or sensations.

**Figure 4 fig4:**
[figure not shown]
Pulsed electromagnetic field (PEMF) therapy.

#### ECHT + PEMF therapy + exercise group

After the 30-min routine exercise, participants in this group will receive ECHT and PEMF therapy for 30 min simultaneously (Figure 5). Then, the application of the gauze and bandages for ECHT will be kept in place for 6–8 h as in the ECHT group.

**Figure 5 fig5:**
[figure not shown]
Combined external Chinese herbal therapy (ECHT) and pulsed electromagnetic field (PEMF) therapy.

### Outcome measures

All demographic information (e.g., age, gender and affected side, etc.) will be collected at baseline assessment session. All outcome assessments will be performed by a blinded assessor in each hospital on three occasions, i.e., at baseline, within 1-week after the completion of intervention, and at a 4-week follow-up.

#### Primary outcomes

*Pain:* overall average pain severity in the past week will be measured via an 11-point visual analog scale (VAS) with terminal descriptors of “no pain” (score 0) and “worst pain possible” (score 10) (30). The minimum clinically important difference of NPRS was shown to be 1.8 (31, 32).

*Overall function:* the Western Ontario and McMaster Universities (WOMAC) Osteoarthritis Index (Likert version 3.1) will be used to measure the overall function in the past week (33). A total of 24 questions are divided in three categories assessing pain, stiffness and physical function, with Likert response options ranging from 0 (none), 1 (mild), 2 (moderate), 3 (severe), to 4 (very severe). A higher score indicates more intense pain, stiffness and physical dysfunction. Though WOMAC is a self-report, disease-specific instrument, excellent test–retest reliability (ICC = 0.83) and convergent validity (Pearson’s r = 0.77) have been demonstrated (34, 35).

#### Secondary outcomes

*Muscle strength*: the manual muscle test (MMT) will be used to test the muscle strength of flexor and extensor in knee and hip.

*Range of Motion (ROM)*: the goniometer will be used to measure the active and passive flexion and extension ROM in hip, knee, and ankle joint.

*Alignment:* the Q angle will be measured via the X-ray.

*Joint space:* the joint space will be quantified by X-ray.

*Cytokines in serum:* TNF-*α*, interleukin-1β (IL-1β), interleukin-15 (IL-15), C1q/tumor necrosis factor-related protein-9 (CTRP9), and interleukin-29 (IL-29), CRP, hs-CRP, MMP-3, MMP-13, HA, NO, MDA, PGE-2.

*Cytokines in synovial fluid:* interleukin-34 (IL-34), interleukin-37 (IL-37), and interleukin-6 (IL-6).

### Sample size

GPower 3.1 software (Heinrich-Heine-Universitat, Dusseldorf, Germany) was used to estimate the sample size. Wang et al. (36) 8-week traditional Chinese herbs hot compress (TCHHC) trial demonstrated a significant interaction on the total WOMAC score between the TCHHC combined with therapeutic exercise group and the therapeutic exercise alone group, yielding a partial eta-squared (
$\eta_{p}^{2}$
) of 0.148, corresponding to an effect size of *f* = 0.416 (36). A conservative approach was adopted for our sample size estimation, considering the comparison of two distinct treatment factors—ECHT and PEMF—and their combined application, alongside a reduced intervention duration of 4 weeks. Employing a 4 (group factor) × 3 (time factor) RM ANOVA framework, and assuming a small effect size (*f* = 0.15), a significance level (*α*) of 0.05, statistical power of 0.80, and accounting for a 15% attrition rate, the total sample size required was 124 participants, evenly distributed across the four groups, i.e., 31 in each group. The sample size is expanded by 10% compared to the original registration in the Chinese Clinical Trial Registry. This modification was necessitated by a post-initiation adjustment to the attrition rate assumption, which was revised upward to a more conservative 15% based on emerging data from the ongoing trial.

### Withdrawal and adverse events

All the intervention methods in this trial are very safe, however, if participants show irreversible intervention-related adverse events during the trial, such as nausea, dizziness, disorientation, or fatigue, the trial will be stopped by the participant and registered. Moreover, this study will strictly comply with the clinical operation and internationally recognized legal requirements. Any adverse events will be reported directly to the ethics committee immediately, and the intervention regimen will be adjusted accordingly after each adverse event. There is no anticipated harm or compensation for trial participation. In addition, the following measures will be undertaken to achieve the best intervention environment: (1) during the 4-week intervention, an individualized intervention plan will be made for each participant on a weekly basis, and the intervention schedule will be adjusted according to the actual conditions of the participant; (2) close attention will be paid and regular feedback will be given to the participants during intervention; (3) the intervention effect on participants during the intervention will be evaluated weekly; and (4) participants’ decision to withdraw from the study will be supported.

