### Statistical analysis

Data entry will be performed by two independent researchers so that the accuracy of the input data can be cross-checked. The Statistical Package for Social Sciences (SPSS) version 26 will be used to conduct the data analysis. Intention-to-treat analysis will be performed. The normality of the data will be checked using the Shapiro–Wilk test. To compare the baseline characteristics of the four groups, one-way ANOVA (or its nonparametric equivalent: Kruskal–Wallis test) or Chi-square tests will be used, depending on whether the criteria for parametric statistics are fulfilled. Those relevant variables that show important between-group differences will be entered as covariates for subsequent analysis. To compare the treatment effects of the 4 intervention approaches, multivariate 4 × 3 ANOVA or ANCOVA with repeated measures (mixed design; repeated factor: time; between-subject factor: group) will be used to determine the time effect and treatment × time interaction effect for each outcome variable of interest. The Greenhouse–Geisser correction will be applied if the assumption of sphericity is violated. If significant results are found, *post-hoc* multiple comparisons of group effects and contrast analyses of time effects will be performed. Bonferroni adjustment will be performed in *post-hoc* analysis to account for the increased risk of Type I errors associated with multiple comparisons. If the criteria for parametric statistics are not fulfilled, the Mann–Whitney test and Wilcoxon test will be used.

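### The adverse-event stopping rule ends the trial for the participant rather than the allocated treatment, which can cost outcome data in a small group selected by harm (minor wording fix)

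*Protocol article*

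**What the plan says.** All references are to the protocol article.

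- **Withdrawal and adverse events** sets a rule that applies "if participants show irreversible intervention-related adverse events during the trial", with nausea, dizziness, disorientation and fatigue as examples. The consequence is that "the trial will be stopped by the participant and registered".
- The same section says of adverse events in general that "the intervention regimen will be adjusted accordingly after each adverse event", and lists among its supportive measures that a participant's "decision to withdraw from the study will be supported". It calls the interventions very safe and gives no adverse-event rate.
- **Outcome measures** sets assessments at baseline, "within 1-week after the completion of intervention, and at a 4-week follow-up".
- **Statistical analysis** states: "Intention-to-treat analysis will be performed". The model is a 4 (group) × 3 (time) repeated-measures ANOVA or ANCOVA.
- **Sample size** gives 124 participants, 31 per group, with f = 0.15, α = 0.05 and power 0.80, "accounting for a 15% attrition rate".

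**The concern.** Stopping treatment and leaving the trial are different events. An intention-to-treat analysis wants outcomes from everyone randomised, including those who stop treatment early. Here the thing that stops is the trial, although the same section speaks of the intervention regimen and the intervention schedule when it means treatment. Read as written, the sentence ends participation, and nothing elsewhere in the article says that these participants stay in follow-up.

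At stake are the post-intervention and 4-week pain and function scores of people who were harmed by their treatment but could often still complete a VAS and a WOMAC. Such losses are not random, because they are defined by harm, and harm may differ between herbal application, PEMF, their combination and exercise with education. The 15% attrition allowance covers the number of people lost, but not this selection. The analysis would then rest on assumptions about values that could have been measured. Nothing can be recovered from those who withdraw consent to follow-up, so the point concerns only those who would still agree to be assessed.

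**Working it through.** **1. The plan's own figure.** The sample size reproduces. For the group × time interaction, λ = f²·N·m/(1 − ρ), with df₁ = (4 − 1)(3 − 1) = 6 and df₂ = 2(N − 4). Inputs from Sample size are f = 0.15, α = 0.05, 4 groups and m = 3 times. The article gives neither the correlation nor a sphericity correction, so ρ = 0.5 and no correction are assumed.

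- N = 104: λ = 0.0225 × 104 × 3/0.5 = 14.04, power 0.799.
- N = 105: λ = 0.0225 × 105 × 3/0.5 = 14.18, power 0.804.
- 105/0.85 = 123.5, rounded up to 124, as stated.

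**2. Possible shift in an arm mean.** The article gives no adverse-event rate, so a range is assumed: k = 1, 2 or 3 of 31 participants in an arm stop. As a yardstick for how far their mean VAS change might differ from the rest, take the value in Primary outcomes: "The minimum clinically important difference of NPRS was shown to be 1.8". It is quoted there for a numeric rating scale and serves here only to set a scale. If the stoppers' outcomes are missing, the arm mean moves by (k/31) × 1.8:

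| k | k/31 | Shift in arm mean (points, 0-10 scale) |
|---|---|---|
| 1 | 3.2% | 0.06 |
| 2 | 6.5% | 0.12 |
| 3 | 9.7% | 0.17 |

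The shift can go either way. A difference between two arms moves by the same amount if only one arm is affected, and by nothing if both are affected alike. It moves by twice the amount (0.35 at k = 3) only in the extreme case where both arms lose three participants who differ by the full 1.8 points in opposite directions.

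**3. Possible loss of power.** Expected completers are 124 × 0.85 = 105.4, taken as 105. Losses inside the 15% allowance cost no planned power. Suppose 1, 2 or 3 participants were lost beyond it and everyone with incomplete data were dropped, which the article does not state. Power would then be:

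- N = 104: 0.799
- N = 103: 0.795
- N = 102: 0.790

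The fall from 0.804 is at most 0.014.

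**4. Visits at stake.** A participant who stops during treatment has two assessments outstanding, so 1 to 3 stoppers put 2 to 6 visits at risk, out of 124 × 2 = 248 planned after baseline.

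**The case against.** The strongest reply is that the sentence never mentions outcome visits, data collection or exclusion from analysis. It stands under a heading about withdrawal and names the participant as the one who stops, so it may describe voluntary withdrawal. It also follows a remark about the safety of the interventions, so the trial may simply be loose English for the treatment. The intention-to-treat statement points the same way. This part stands: the article does not order that follow-up end, and a reader who infers a deliberate decision to discard these participants goes beyond the text.

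Two further inferences are tempting and not supported.

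- A reader might see a contradiction between adjusting the regimen after every event and stopping after an irreversible one. These can be read as two tiers, a general rule and a specific one for a severe subset.
- A reader might say that someone who stops early never reaches the post-intervention assessment. Interventions fixes the course at 4 weeks, so completion can mean its scheduled end.

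It can also be said that visit procedures after discontinuation belong in the full protocol, which is not shown, so their absence from an article is no fault. That would answer a complaint of silence. It does not answer this one, because the article states a rule and the rule names the wrong thing to stop. If treatment was meant, the correction makes the text say so.

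**Conclusion.** The point holds as a minor one. As written, the rule ends trial participation after an irreversible intervention-related event, can remove outcomes from participants selected by harm, and does not fit an intention-to-treat analysis. Any loss of data depends on sites following the literal wording.

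The likely effect is small. The one-arm shift of 0.06 to 0.17 VAS points is at most about a tenth of the 1.8-point yardstick (0.17/1.8 ≈ 0.097), and it rests on assumed counts and an assumed difference. The power figures rest on ρ = 0.5 and no sphericity correction, and show no material loss. The trigger is narrow, since the event must be both irreversible and related to the intervention, although the listed examples are usually transient symptoms and a site could apply it more widely.

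A reader might infer that the trial's results will be seriously biased, or biased in favour of one arm. The article supports neither: it gives no adverse-event rate, and the direction of any bias is unknown.

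**What to change.** In Withdrawal and adverse events, make the allocated intervention, not the trial, the thing that stops. Add one sentence: these participants keep their scheduled post-intervention and 4-week VAS and WOMAC assessments, timed from the planned end of the 4-week course, unless they withdraw consent to follow-up.

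The cost is the wording change and carrying out up to two already planned visits per affected participant with the existing blinded assessors. The sample size of 124 and the analysis model do not change.
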